# Tailored exercise management (TEMPO) versus usual care for people aged 80 years or older with hip/knee osteoarthritis: study protocol for a feasibility randomised controlled trial

**DOI:** 10.1186/s40814-023-01275-5

**Published:** 2023-04-01

**Keywords:** Over 80-year-olds, Osteoarthritis, Comorbidities, Exercise, Rehabilitation, Adherence

## Abstract

**Background:**

Exercise is recommended for all people with osteoarthritis. However, these recommendations are based on randomised clinical trials including people with an average age between 60 and 70 years, and these findings cannot reliably be generalised to people aged 80 years or older. Rapid loss of muscle occurs after 70 years of age, and older people are more likely to also have other health conditions that contribute to difficulties with daily activities and impact on their response to exercise. To improve care for people aged 80 or older with osteoarthritis, it is thought that a tailored exercise intervention targeting both osteoarthritis and any other health conditions they have, may be needed. The aim of this study will be to test if it is possible to conduct a randomised controlled trial (RCT) for people over 80 years of age with hip/knee osteoarthritis of a tailored exercise intervention.

**Methods:**

A multicentre, parallel, 2-group, feasibility RCT with embedded qualitative study, conducted in ≥ 3 UK NHS physiotherapy outpatient services. Participants (*n* ≥ 50) with clinical knee and/or hip osteoarthritis and ≥ 1 comorbidity will be recruited by screening referrals to participating NHS physiotherapy outpatient services, via screening of general practice records and via identification of eligible individuals from a cohort study run by our research group. Participants will be randomised (computer-generated: 1:1) to receive either: a 12-week education and tailored exercise intervention (TEMPO); or usual care and written information. The primary feasibility objectives are to estimate: (1) ability to screen and recruit eligible participants; (2) retention of participants, measured by the proportion of participants who provide outcome data at 14-week follow-up. Secondary quantitative objectives are to estimate: (1) participant engagement assessed by physiotherapy session attendance and home exercise adherence; (2) sample size calculation for a definitive RCT. One-to-one semi-structured interviews will explore the experiences of trial participants and physiotherapists delivering the TEMPO programme.

**Discussion:**

Progression criteria will be used to determine whether a definitive trial to evaluate the clinical and cost-effectiveness of the TEMPO programme is considered feasible with or without modifications to the intervention or trial design.

**Trial registration:**

ISRCTN75983430. Registered 3/12/2021. https://www.isrctn.com/ISRCTN75983430.

**Supplementary Information:**

The online version contains supplementary material available at 10.1186/s40814-023-01275-5.

## Background

Osteoarthritis (OA) of the hip and knee is the 11th leading cause of disability worldwide [1], and the most common joint disease in the United Kingdom (UK) [2]. The prevalence of hip and knee OA has a strong association with increasing age [3]. In the UK alone, approximately 3 million people were aged 80 or older in 2018, and this group is projected to increase to almost 6 million by 2043, making it the fastest growing population group [4]. Adults aged 80 years or older are the least physically active and have the highest healthcare expenditure [5, 6].

The presence of comorbidities is also increasingly common with age, with over 80% of people aged 85 years or older having two or more chronic conditions [7]. It has been suggested that management of patients with multiple conditions is now the most important task facing health services in developed countries [8]. The most common conditions among people with hip/knee OA include cardiovascular diseases, depression, type 2 diabetes, hypertension and other sites of musculoskeletal pain [9–11].

Current evidence-based guidelines recommend exercise for all patients with hip/knee OA, regardless of age, pain levels, disease severity, or functional ability [2, 12–14]. However, these recommendations are based on data from randomised trials commonly conducted in patients aged between 60 and 70 years [15, 16]. In Cochrane reviews of exercise for hip [16] and knee OA [15], no trials involved participants with an average age over 80. Between 70 and 80 years of age, many physiological changes occur, and people have a broad range of abilities at this age. Muscle strength declines 10 to 15% between 60 and 70 years of age, after which the loss accelerates to 25 to 40% between 70 and 80 years of age [17, 18]. In addition, endurance capacity declines approximately 10% between 70 and 80 years of age [19]. Given these changes, exercise recommendations from younger populations cannot reliably be generalised to adults aged 80 or older. Comorbidities may also interfere with the use of exercise among people with hip/knee OA. Current OA guidelines do not offer specific recommendations for comorbidity-associated exercise adaptions.

In clinical practice, over 42% of people aged over 75 years in the UK consult a General Practitioner (GP) regarding their OA [20], but they are significantly less likely to be referred for exercise than younger people [21]. This may reflect uncertainty around exercise prescription for this patient group, particularly in the presence of comorbidities [22], lack of existing suitable exercise interventions or settings, or reluctance from patients to engage in exercise [23].

The UK National Institute for Health and Care Excellence (NICE) have identified treatments for OA in very old people as a research priority, specifically the acceptability, nature, and setting for exercise strategies for this population [2]. NICE guidelines, and the 2019 Copenhagen Consensus statement on physical activity and ageing also highlight the need for tailored strategies that consider comorbidities in any approach to exercise for older people [24, 25].

The overall aim of the ‘Tailored Exercise Management for People aged 80 years or older with hip/knee Osteoarthritis’ (TEMPO) trial is to evaluate whether it is feasible to conduct a definitive multicentre RCT to test the clinical and cost-effectiveness of a tailored exercise intervention, compared to usual care, in improving functional status in adults aged 80 years and over with hip/knee OA and comorbidities.

Specifically, our primary objectives are to assess participant recruitment to, and retention in, the trial. Key secondary objectives are to determine participant engagement with the study and feasibility of the interventions from participant and physiotherapist (intervention provider) perspectives; to estimate the sample size calculation for a definitive trial, and to determine experiences and perceptions of the study design and intervention from both participant and physiotherapist perspectives.

## Methods/design

### Trial design

A multicentre, parallel, 2-group, feasibility randomised (1:1) controlled trial with embedded qualitative study (outlined in Fig. 1). A schedule of enrolment, interventions, and assessments is presented in Table 1.

**Fig. 1 Fig1:**
[figure not shown]
Study flow chart

**Table 1 Tab1:** Schedule of enrolment, interventions, and assessments for the TEMPO study

	Pre-randomisation	Baseline Assessment	Intervention period (0–14 weeks)	14-week Assessment	16–18 weeks after randomisation
Enrolment					
Potential participant identification and screening	X				
Provision of PIS	X				
Eligibility assessment	X				
Informed consent	X				
Assessment					
Demographics		X		X	
Nottingham Extended Activities of Daily Life Scale (NEADL)		X		X	
EuroQol EQ-5D-5L		X		X	
Average, worst and walking hip/knee pain (0–10 NRS)		X		X	
Nordic pain questionnaire		X		X	
Geriatric Depression Scale (GDS-15)		X		X	
Geriatric Anxiety Scale (GAS10)		X		X	
ProFANE self-report of falls and fall related injuries		X		X	
Walking confidence: single item from Modified Gait Self-Efficacy Scale		X		X	
Short Physical Performance Battery (SPPB)		X		X	
Current medications		X			
Attendance-treatment log (TEMPO intervention)			X		
Adherence-home exercise diary (TEMPO intervention)			X		
Adverse events recorded			X	X	
Additional treatments received				X	
Postal/phone collection of core outcomes (if required)					X
Qualitative interviews with sample of participants					X
Interventions					
Provision of hip/knee OA booklet (usual care)		X			
Referral to TEMPO physiotherapist		X			
TEMPO programme: 4–8 individual sessions with physiotherapist			X		

### Setting

Potentially eligible participants will be identified from referrals to participating NHS physiotherapy outpatient services, via screening of general practice records and via identification of eligible individuals from a cohort study run by our research group [26]. Interventions will be delivered within physiotherapy outpatient services at a minimum of three NHS sites across England.

### Eligibility criteria

The target population is adults aged 80 years or older with clinical knee and/or hip OA and at least one comorbidity. Full eligibility criteria are listed in Table 2.

**Table 2 Tab2:** Eligibility criteria

Inclusion criteria
Registered with a primary care practice
≥ 80 years of age
Knee and/or hip osteoarthritis. GP register check (hip/knee osteoarthritis diagnosis recorded) or self-report of knee or hip joint pain lasting 3 months or longer AND knee or hip joint pain on most days of the past month
≥ 1 comorbidity. GP register check and/or self-report
Individual is willing and able to give informed consent for participation in the study
Exclusion criteria
Has a terminal condition with a life expectancy of less than 6 months or under palliative care
Any substantial health or social concern that, in the opinion of the inidividual’s GP, would place the individual at increased risk or inability to participate including known inability to provide informed consent
Significant cognitive impairment. GP check and/or assessed by research clinician. Eligibility screen includes the 6-item Cognitive Impairment Test (score of 8 or more are ineligible)
Unable to walk 3 m with or without an aid
Presents with signs of serious pathology requiring immediate referral for investigations
Unable to follow verbal or written instructions including inability to follow simple safety instructions

We have chosen to include participants with any comorbidities. Exercise adaptions are included in the intervention for comorbidities that we identified were both common among people with hip/knee OA and had a significant impact on function and/or mobility. We will assess which comorbidities participants report, and for the definitive trial will consider if additional comorbidity adaptions are required, or if participants with only specified comorbidities should be included.

### Participant identification

Three methods will be used to identify potential participants, informed by evidence that this population are often not referred to physiotherapy [21].

#### Screen of physiotherapy referrals

Physiotherapy referrals received by the NHS outpatient sites who will be providing the trial assessments and intervention delivery will be screened to identify adults aged 80 years and older with hip or knee pain potentially due to OA.

#### Identification of general practice consulters

We will work with the Clinical Research Network (CRN) to identify GP practices who have existing referral pathways to the NHS sites who will be providing the trial assessments and intervention delivery who are willing to take part in identifying and inviting potential participants. Electronic records of participating general practices will be screened to identify adults aged 80 years and over who have consulted a GP with knee and/or hip pain consistent with OA in the previous 36 months, and who have at least one other comorbidity, using Read/Systematized Nomenclature of Medicine (SNOMED) codes. The participating GP will screen the list and exclude any individuals who have any substantial health or social concern that, in their opinion, would place the individual at increased risk or inability to participate.

#### Screening of existing cohort study

The Oxford Pain, Activity and Lifestyle (OPAL) study is a prospective longitudinal cohort study of community-dwelling older adults aged 65 years or older recruited from 35 general practices across England. A detailed profile is published [26]. OPAL participants from GP practices who have existing referral pathways to the NHS sites who will be providing the trial assessments and intervention delivery who meet the inclusion criteria and have given permission to be contacted about participating in other studies will be identified and invited by the OPAL study team.

### Screening

Individuals who have been identified as potentially eligible to participate in the trial from one of the three methods described above will be mailed a covering letter and the Participant Information Sheet (PIS). If interested in participating, they will be asked to return a registration of interest form. A member of the trial team will then telephone the potential participant to check initial eligibility and answer any questions. If the person is potentially eligible, and, if they are willing to proceed, the researcher will invite them to a research clinic assessment at their closest participating NHS site.

#### Confirmation of eligibility assessment

Confirmation of eligibility will be undertaken at the research clinic assessment, by an experienced musculoskeletal physiotherapist. This assessment will include the 6-item Cognitive Impairment Test and red flag screening. The 6-item Cognitive Impairment Test is a brief screening tool for cognitive impairment, recommended for use in primary care [27]. Scores of 0–7 are considered normal and ≥ 8 significant. Participants who score ≥ 8 will not be eligible to participate in the trial, and their GP will be notified of the finding. Red flag screening will assess for signs of serious pathology requiring immediate referral for investigation.

### Consent

Prior to any study-related procedures or data being collected, written informed consent will be obtained. Permission from the participants will also be obtained to inform their GP of their inclusion in the study. The person who obtains the consent will be suitably qualified and experienced and have been delegated to do so by the site Principal Investigator.

### Randomisation, blinding, and allocation concealment

Following consent, participants will be randomised to the TEMPO intervention or Usual Care in a 1:1 ratio using the centralised web-based randomisation service provided by the Oxford Clinical Trials Research Unit (OCTRU). Randomisation will be stratified by centre. Randomisation will be completed in real time within the research clinic appointment after baseline data has been obtained. On randomisation of a participant, the central trial team and main site contact will be notified via an automated email.

By virtue of the design, it is not possible to blind participants or the physiotherapists delivering the intervention. The local researcher clinicians conducting the assessments will not be blinded as they will undertake randomisation, arrange referral to the TEMPO intervention and provide the usual care information leaflet. The trial statistician who will be performing analysis of the data collected will also not be blinded to treatment allocation.

### Interventions

#### Comparator: usual care

Treatment for participants in the usual care group will vary depending on their method of identification. Participants randomised to the usual care intervention who are identified via existing referrals to NHS physiotherapy outpatient departments will be treated as usual by a physiotherapist who has not been trained in the TEMPO intervention. Participants randomised to the usual care intervention who are identified by screening of GP records, or screening of participants in the OPAL cohort study will continue to be managed by their GP. Participants in the usual care intervention will be given an educational booklet produced by Versus Arthritis [28, 29] at the conclusion of their baseline research clinic assessment.

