### Sample size determination

As this is a feasibility study which is not aimed to assess treatment effects, we have not undertaken a formal power sample size calculation. A minimum of 50 participants will be recruited, based on Teare et al.’s [46] recommendation that between 50 and 70 are required when continuous scale data outcomes are to be collected. Achieving this sample size will require an average estimate of 2 participants per month per site, over the 9-month recruitment period. This sample size will also provide sufficient data to answer our feasibility objectives. Outcome data for the NEADL will be used to estimate standard deviations and CIs of the treatment estimates which will be used to inform a sample size calculation for a definitive trial.

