### Statistical methods

The primary analysis will evaluate the feasibility of conducting a future definitive multicentre RCT. Descriptive statistics of the following feasibility outcomes will be reported: recruitment screening logs, consent forms, and logs of data collection forms; TEMPO intervention session attendance, home exercise adherence, treatment/s received by usual care group, attrition rate, safety reporting forms; follow-up participant questionnaire (and clinical assessment) completion rates of those randomised.

Outcome measures will be reported descriptively and differences between treatments for the Intention To Treat (ITT) population will be reported together with 95% confidence intervals (CI). Withdrawals from treatment or the trial, related AEs and SAEs will be reported. Mean and standard deviation or median and interquartile range will be used for continuous variables and counts, and numbers and percentages will be used for any binary or categorical variables. Missing data will be minimised by careful data management. No comparative statistical testing will be undertaken as the study is not powered for this purpose.

Additional analyses will evaluate the proposed primary and secondary outcomes planned for the full trial. The planned primary outcome for the full study, NEADL, will be measured and reported at baseline and 14-week follow-up for each intervention group. The difference in the means between the intervention group compared to usual care together with the corresponding 95% CI will be reported. Analysis of the primary outcome will be performed using multivariate linear regression with adjustment for the baseline NEADL score, number of comorbidities reported and stratification factor: centre. Analysis methods for the primary outcome will be conducted for secondary outcomes, with logistic regression being used for binary outcomes and linear regression for continuous ones. No statistical tests will be performed as the study would not be powered to detect any differences.

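### Usual care is physiotherapy or GP management depending on identification route, but the NEADL analysis reports one pooled difference with no allowance for route

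*Protocol article*

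**What the plan says.** Three parts of the protocol article bear on this.

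- **Comparator: usual care.** The section says that "Treatment for participants in the usual care group will vary depending on their method of identification". Controls identified from existing physiotherapy referrals "will be treated as usual by a physiotherapist who has not been trained in the TEMPO intervention". Controls identified from GP records or from the OPAL cohort "will continue to be managed by their GP". All controls also receive an educational booklet.
- **Randomisation, blinding, and allocation concealment.** The ratio is 1:1 and "Randomisation will be stratified by centre". No other factor is named.
- **Statistical methods.** The NEADL difference is reported with a 95% CI from a linear regression with "adjustment for the baseline NEADL score, number of comorbidities reported and stratification factor: centre". The same approach is carried to the secondary outcomes. Route is not in the list and no estimate by route is described.

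Under Sample size determination, "Outcome data for the NEADL will be used to estimate standard deviations and CIs of the treatment estimates", and these feed the sample size of the definitive trial. The same section says "A minimum of 50 participants will be recruited". The treatments that controls actually receive are recorded at 14 weeks (Content of the usual care intervention) and summarised descriptively (Statistical methods).

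**The concern.** Identification route is settled before randomisation, and it decides which of two control conditions a participant would receive. The plan therefore contains two randomised comparisons: TEMPO against usual physiotherapy, and TEMPO against continued GP management. It reports them as one number. The weights in that average are the shares of participants who arrive by each route, and the article neither sets nor forecasts those shares.

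This matters because the study exists to plan a definitive trial against usual care. If that trial recruits with a different route mix, or settles on one comparator, the pooled difference and its CI describe a contrast that the trial will not be testing. The article fixes both the stratification factor and the covariate list, so this is a stated analysis choice and not a detail left to an unseen analysis plan.

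**Working it through.** **Inputs from the article.** At least 50 participants, 1:1, so about 25 per arm; at least three sites; 2 participants per site per month for 9 months; stratification by centre; covariates baseline NEADL, number of comorbidities and centre.

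**Assumed inputs (none is in the article).** p is the physiotherapy-referral share. g is the difference in mean NEADL between routes, in within-route SDs. d_GP and d_PT are the TEMPO effects against GP management and against physiotherapy, in SDs. The definitive trial has 90% power at two-sided 5%.

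**Step 1. The plan's own figure.** 50 / (3 × 9) = 1.85 per site per month, which rounds to the stated 2; conversely 2 × 3 × 9 = 54, which meets the floor of 50. This is consistent. There is no power calculation to reproduce.

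**Step 2. The mixed contrast.** Pooled effect = (1 − p) × d_GP + p × d_PT, and n per arm ≈ 2 × (1.960 + 1.282)² / effect². With d_GP = 0.4 and d_PT = 0.2:

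| p | Pooled effect (SD) | n per arm |
|---|---|---|
| 0.2 | 0.8 × 0.4 + 0.2 × 0.2 = 0.36 | 163 |
| 0.5 | 0.5 × 0.4 + 0.5 × 0.2 = 0.30 | 234 |
| 0.8 | 0.2 × 0.4 + 0.8 × 0.2 = 0.24 | 365 |

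Against GP management alone (0.4 SD) the figure is 132 per arm. With d_PT = 0, p = 0.2 gives 0.32 SD and 206 per arm, and p = 0.5 gives 0.20 SD and 526 per arm. If d_PT equals d_GP, the route mix does not move the effect at all.

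**Step 3. Chance imbalance in route.** Fix the total on the referral route at K = 50p and let the number in one arm be hypergeometric (25 drawn from 50), ignoring centre strata. The probability that the referral share differs between arms by at least 20 percentage points is:

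- p = 0.2 (K = 10): 7%
- p = 0.3 (K = 15): 22%
- p = 0.5 (K = 25): 26%

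Treating the two arms as independent binomials gives 11% at p = 0.2 and 20% at p = 0.5. The figures differ partly because so few values are possible: with K = 10, the smallest gap that reaches 20 points is 6/25 = 24 points.

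The effect of such an imbalance is modest. A 20-point gap with g = 0.3 to 0.5 shifts the unadjusted difference by 0.20 × 0.3 = 0.06 to 0.20 × 0.5 = 0.10 SD. The unadjusted 95% CI half-width at 25 per arm is 2.01 × √(2/25) = 0.57 SD.

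**Step 4. The NEADL SD.** Pooling multiplies the SD by √(1 + p(1 − p)g²).

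- p = 0.2, g = 0.2: √1.0064 = 1.003
- p = 0.5, g = 0.5: √1.0625 = 1.031
- p = 0.5, g = 0.8: √1.16 = 1.077

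From chi-square limits on n − 2 degrees of freedom, the 95% CI for an SD runs from 0.83 to 1.25 times the estimate with 50 participants, and from 0.82 to 1.28 times with 42 (about 85% of 50). The inflation is well inside that.

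**Step 5. What by-route estimates can deliver.** Controls on the referral route number about 25 × 0.2 = 5 to 25 × 0.5 = 12.5. With 5 per arm the unadjusted half-width is 2.31 × √(2/5) = 1.46 SD; with 12 per arm it is 2.07 × √(2/12) = 0.85 SD. These can describe, but cannot separate the two contrasts.

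**The case against.** The case on the other side has real force.

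- **Purpose.** The article says the study does not aim to assess treatment effects and that no tests will be done. No criterion in Table 3 (Progression criteria) uses the NEADL difference. This stands, and it confines the harm to planning the definitive trial. It does not remove the harm, because Sample size determination sends the CIs of the treatment estimates into that planning.
- **Disclosure.** The varying comparator is stated openly, usual-care content is a feasibility outcome, and the interviews cover recruitment methods and study design. Learning what usual care is before fixing a comparator is a fair use of a feasibility trial. This stands too, but nothing stated links the recorded content to route or to the NEADL difference.
- **Stratification.** With about 50 participants and at least three centres, stratifying by centre alone is defensible. This stands.
- **A route covariate does not separate the contrasts.** A main effect for route deals with balance and residual variance and still returns one averaged effect. This is correct, so by-route reporting has to come first.

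A reader might infer three stronger things that the article does not support. The first is that leaving route out biases the comparison. It does not: allocation is randomised, so chance imbalance adds noise, and the planned covariates may absorb part of it. The second is that pooling makes the NEADL SD unusable, which Step 4 does not bear out. The third is that consent and retention will be reported only pooled over route. The article is silent on that, and such breakdowns are commonly left to the full protocol or analysis plan.

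**Conclusion.** The point holds as a limit on what the pooled NEADL difference means. It is an unbiased estimate for this sample's route mix, but it averages TEMPO against physiotherapy and TEMPO against GP management with weights that the plan leaves open. How much that matters depends on how far the two effects differ, which the article does not say. Under the illustration of 0.4 and 0.2 SD, the implied definitive size runs from 163 to 365 per arm as the referral share goes from 20% to 80%; if the two effects are equal, the mix has no influence on it.

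The other two consequences are secondary. A route imbalance of at least 20 points has a probability of about 7% to 26% for assumed referral shares of 20% to 50%, ignoring centre strata. SD inflation is about 0.3% to 3% for route differences of 0.2 to 0.5 SD. This is a cheap improvement to a stated analysis and not a flaw that threatens the trial.

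**What to change.** In Statistical methods:

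1. Report the NEADL difference with its 95% CI, and the NEADL mean and SD by arm, separately for physiotherapy referral and for GP record/OPAL, beside the pooled estimate. Label the by-route results as descriptive. Each within-route comparison is still randomised. A difference between the routes is not, since the people as well as the comparator may differ.
2. Add route as a binary covariate in the pooled NEADL and secondary-outcome models.
3. Report consent, 14-week retention and usual-care content by route.
4. When the definitive sample size is derived, state which comparator, or which route mix, it refers to.

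Adding route to the stratification is not required, and recruitment was already under way when the article was published.

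The cost is one degree of freedom in the pooled models and a few extra table rows. The by-route estimates will be very imprecise, with about 5 to 12 controls on the physiotherapy route if its share is 20% to 50%, and should not be used to choose between comparators on their own. No new patient assessment is needed: route must be known for each participant because usual care depends on it. The article does not say that the screening log records route, so confirm that it is captured in the trial data.

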### Concurrent healthcare for all participants

All participants will be advised that they can continue to access usual healthcare, including medications and consultations with other health professionals. Details of cointerventions will be recorded at the 14-week assessment.

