##### Content of the usual care intervention

Details of treatments received will be recorded by the Research Clinician at 14-week Research Clinic Assessment.

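### The rule keeping usual-care participants away from TEMPO-trained physiotherapists covers only the physiotherapy-referral route, leaving a small opening for crossover among controls from GP records and OPAL

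*Protocol article*

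**What the plan says.** The protocol article sets usual care by how the participant was identified (Comparator: usual care). Controls found through existing physiotherapy referrals "will be treated as usual by a physiotherapist who has not been trained in the TEMPO intervention". For the other two routes, the same paragraph says that controls found by screening GP records or "screening of participants in the OPAL cohort study will continue to be managed by their GP". It adds no condition on who treats them if that GP refers them to physiotherapy.

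Both of these routes are tied to the trial sites. Participating practices are those with "existing referral pathways to the NHS sites who will be providing the trial assessments and intervention delivery" (Identification of general practice consulters). The cohort route draws on "OPAL participants from GP practices who have existing referral pathways to the NHS sites" (Screening of existing cohort study). TEMPO itself is given in the outpatient physiotherapy departments of the participating trusts (TEMPO intervention).

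Care outside the trial is not restricted: participants are told that "they can continue to access usual healthcare, including medications and consultations with other health professionals" (Concurrent healthcare for all participants).

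On measurement, the control arm has its own secondary feasibility outcome: "Details of treatments received will be recorded by the Research Clinician at 14-week Research Clinic Assessment" (Content of the usual care intervention). Table 1 lists additional treatments at 14 weeks, the section on the 14-week assessment has the research clinician record cointerventions, and Statistical methods lists the treatments received by the usual care group among the descriptive results.

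**The concern.** By requiring an untrained physiotherapist for one group of controls, the plan treats crossover as a risk worth controlling. The other two groups can reach the same departments through their GP, and the requirement does not follow them there. Followed as written, nothing stops a control from the GP or OPAL route who is referred during follow-up from being booked with someone trained to deliver TEMPO.

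Two uses of the trial are touched. First, the article reports an adjusted between-group NEADL difference with its confidence interval, and uses NEADL data to inform the sample size of the definitive trial (Sample size determination; Statistical methods). Controls who receive TEMPO-like care would tend to pull that difference towards zero. Second, whether two individually randomised arms can be kept apart within one department is itself something a feasibility trial should learn.

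**Working it through.** The point rests on text, and the plan gives no figure to reproduce. The passages side by side:

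| Route | Who manages a control | Refers to the TEMPO sites? | Untrained physiotherapist required? |
|---|---|---|---|
| Physiotherapy referral | Physiotherapist | Already referred there | Yes |
| GP records | GP | Yes, by selection of practices | Not stated |
| OPAL cohort | GP | Yes, by selection of practices | Not stated |

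**What the record can show.** Treatments received by controls are captured at 14 weeks and reported. Clinician details and session content are described only for TEMPO sessions (Treatment logs). The article does not say that the record for controls notes the provider's training.

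**How many controls.** With a minimum of 50 randomised 1:1, there are about 50 / 2 = 25 controls. The article gives no referral rate, so all three shares below are assumptions:

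- s, the share of controls from the GP or OPAL route: 0.50 to 1.00
- r, the share of those referred to physiotherapy within 14 weeks: 0.05 to 0.20
- t, the share of those referred who see a trained physiotherapist: 0.25 to 0.50

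Expected crossovers = 25 × s × r × t.

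- Low: 25 × 0.50 × 0.05 × 0.25 = 0.16, or about 0.2 of a person (c = 0.6% of controls)
- Middle: 25 × 0.75 × 0.10 × 0.50 = 0.94 (c = 3.75%)
- High: 25 × 1.00 × 0.20 × 0.50 = 2.5 (c = 10%)

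**What that does to the contrast.** If a share c of controls received the whole TEMPO effect, the contrast would fall to (1 − c) of its value, and the sample size needed in the definitive trial would rise by 1 / (1 − c)².

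| c | Contrast left | Sample-size factor |
|---|---|---|
| 0.6% (low) | 99.4% | 1 / 0.99375² = 1.01 |
| 3.75% (middle) | 96.25% | 1 / 0.9625² = 1.08 |
| 5% | 95% | 1 / 0.95² = 1.11 |
| 10% (high) | 90% | 1 / 0.90² = 1.23 |
| 20% | 80% | 1 / 0.80² = 1.56 |

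The last row would need 5 of 25 controls to cross over, twice the top of the assumed range. Every factor is an upper bound for its c, because each crossover is taken to receive the full effect.

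**The case against.** The strongest reply is that the article attaches the condition to the only controls for whom physiotherapy is planned, and is merely silent about a contingency that local booking could handle. Sites know who is in which arm: the research clinician carries out the randomisation and the main site contact is notified by email. That is fair, but the article does not say that bookings use this information. Because it states the rule and its scope, this is more than a detail lost in condensing.

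A second reply is that crossover will be rare. The article itself says that older people are less often referred for exercise (Background) and that this is why three identification routes are used (Participant identification). A crossover needs a new referral, an appointment and a trained physiotherapist, all within 14 weeks. This stands, and points to the lower end of the range.

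Third, seeing a trained physiotherapist is not the same as receiving TEMPO, which is a course of four to eight sessions with a workbook, diary and equipment. Ordinary physiotherapy is also legitimate usual care here. This stands too, and is why the factors are only upper bounds.

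A reader might go further and infer that crossover goes unmeasured. The documents do not support that. Physiotherapy given to controls would be recorded at 14 weeks and reported. What is open is whether the record identifies a TEMPO-trained provider, and that item may sit in the case report form or full protocol, which are not shown.

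**Conclusion.** The gap in the safeguard is real on the text: one of three identification routes is covered, and the two uncovered routes lead by design to the departments that deliver TEMPO. That the record may not separate TEMPO-trained from ordinary providers is a secondary point, because it depends on forms not seen.

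Severity is minor. About 0.2 to 2.5 of 25 controls would be expected to cross over, on assumed shares that the article neither gives nor contradicts. A reader might take the inflation factors as a forecast for the definitive trial. They are not one: they rest on assumed shares and on full TEMPO exposure in every crossover. There is no efficacy test here, and none of the four progression criteria in Table 3 depends on the NEADL difference. What remains at stake is the NEADL estimate carried forward and the evidence on whether the arms can be separated within shared departments.

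**What to change.** In Comparator: usual care, apply the existing condition to every usual-care participant whatever the identification route, so that any referral to a participating department before the 14-week assessment is booked with a physiotherapist not trained in TEMPO. This leaves access to physiotherapy unchanged and constrains only the provider, as is already done for the referral route.

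As a secondary step, if the form does not already do so, note in the 14-week treatments-received record whether the provider was TEMPO-trained, and report the count of such controls.

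The cost is one sentence, at most one form item and a small booking constraint for a few people. Departments already need an untrained physiotherapist for controls from the referral route.
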